#### Data collection for and definition of covariates

A number of patient demographic and clinical characteristics could affect the frequency of vital sign determinations and laboratory tests for glucose or lipids. For example, patients with chronic heart failure should have weight recorded frequently; patients with diabetes would have more frequent fasting plasma glucose tests; and older patients and patients that have frequent primary care visits for any reason would also be more likely to meet criteria for recommended metabolic monitoring. Therefore, in addition to birth date, gender and race, we will extract diagnostic codes to identify pre-existing diagnoses of overweight/obesity, diabetes or dyslipidemia, as well as other physical comorbidities. These variables, summarized over site, will be included as covariates in the statistical models of monitoring and management.

#### Assessing organizational readiness-to-change

The effect of organizational readiness-to-change on implementation is being measured in this study with the Organizational Readiness to Change Assessment (ORCA) [46]. This instrument was developed for use in VA treatment settings, assessing organizational readiness in terms of PARIHS domains of evidence, context and facilitation, as well as the sub-elements of culture and leadership [47,48]. The 15- to 20-minute survey was administered to all provider participants at the 12 participating sites during the Pre-implementation Phase and will be repeated at the conclusion of the Sustainability Phase.

#### EBQI/F intervention costs

To estimate direct intervention costs (Objective 3), we adapted the methodology used in the Translating Initiatives in Depression into Effective Solutions (TIDES) study [44]. We will explore potential variations in intervention costs at sites with lower versus higher organizational readiness-to-change. We will assign costs to one of three categories of implementation activities, as shown in Table 2.

**Table 2 T2:** Intervention costs for EBQI/F implementation activities

**Activity category**	**Examples of activities included**
**Implementation design**	In-person EBQI design meeting
	Introductory educational conferences by experts on research team
	Meeting preparation
**Clinical informatics**	Preparation of site feedback reports
	Customization of VA computer routines based on EBQI/F site visit requests
	Installation, pilot testing, and refinement of VA computer routines
**Facilitation**	External facilitation activities, including communication with site participants, coordinating technical assistance, troubleshooting, and problem-solving

### Data analysis

Because weight gain is a common antipsychotic side effect that increases risk of diabetes and cardiovascular disease [6,9,11], and overweight/obesity is prevalent in patients with psychotic disorders [10,11], the primary outcome measures for the proposed project will be the extent to which weight/BMI is monitored and to which overweight or obese patients receive a guideline-concordant weight management intervention. At each site, the proportion of patients who receive baseline monitoring, follow-up monitoring, and management of metabolic abnormalities will be measured each month against those who were due for such actions during the same time period. We expect EBQI/F intervention sites to gradually increase performance on monitoring and management measures over time. Therefore, we will conduct a time series analysis of monthly performance, with each site contributing six monthly performance measures in each of the three phases of the study. These analyses will estimate the change in rates of baseline monitoring during the Implementation Phase due to intervention (national quality improvement initiative with and without EBQI/F), and allow comparison of these performance changes between sites receiving EBQI/F and those not. Further, these analyses will allow within-phase changes in monitoring rates to be compared between phases; *e.g*., for EBQI/F sites, is the monitoring performance change during the Implementation Phase different from that during the Sustainability Phase? We will similarly collect, summarize, and analyze data from all patients due for follow-up metabolic monitoring and metabolic management (as defined in Table 1) during the three study phases.

We will compare the performance change over time (a slope) between EBQI/F and control sites using a random coefficients regression (RCR) that accounts for repeated measures taken within a site (see Additional file 1 for detailed explanation). The random coefficients portion of the RCR accounts for site-to-site variability within an intervention group (*e.g*., EBQI/F); that is, each site has its own slope, but sites within the same intervention group tend to be more alike than those from the other intervention group. The RCR will also allow the slopes to change with the phase of the study, thus allowing us to also test whether performance change differs among the phases over the study. For example, performance change during pre-implementation is expected to be unchanging or flat, but is expected to increase or trend upward once EBQI/F begins.

Descriptive analysis of intervention costs will include calculation of the number of providers involved in each phase of the EBQI/F intervention (person count) and the number of hours spent (person hours), with separate estimates for clinical QI and research team activities. We will also explore whether there may be potentially meaningful variations in costs/intensity of the EBQI/F intervention at the EBQI sites based on their readiness-to-change, using data collected from the ORCA.

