## Methods

This study employs a cluster randomized clinical trial design, with matched pairs of VA facilities defined as the clusters, to test the effectiveness of an EBQI plus facilitation (EBQI/F) intervention combined with the ongoing national quality improvement initiative (MIAMI Project) at six sites (intervention sites) compared to six matched comparison sites exposed to the national quality improvement initiative alone (control sites). The extent to which metabolic monitoring and management recommendations are followed will be examined at the intervention sites over three six-month intervals: the Pre-implementation Phase, defined as the six-month period prior to the initial EBQI site visit at the intervention sites; the Implementation Phase, which includes active external facilitation (EBQI/F); and the Sustainability Phase, during which the research team continues to evaluate the extent of metabolic monitoring and management, but external facilitation is not provided (see Figure 1). Each control site will be examined over the same three six-month periods as the matched intervention site. During the initial site visit, and for a variable period of time following the visit (the EBQI Design Phase), each intervention site’s EBQI participants will work with the facilitator to develop a local implementation plan. If preliminary results indicate that the EBQI/F intervention is successful, control sites will be offered the EBQI/F intervention in a Crossover Phase at the conclusion of the study.

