### EBQI design phase

The EBQI Design Phase includes an initial site visit and subsequent development of a local implementation plan at each site. In this phase, researchers contribute knowledge about the evidence base for clinical care and implementation strategies, providing implementation tools and materials. Clinical stakeholders contribute local knowledge and expertise needed to tailor implementation tools/strategies to match organizational needs, priorities and capabilities.

EBQI participants at each intervention site include approximately two to four key staff (*i.e*., administrative leaders, clinicians, nurses) involved in monitoring and managing patients treated with antipsychotics who were identified based on discussions between the study PI and site mental health leaders.

The EBQI Design Phase includes consideration of site-specific data collected in the developmental formative evaluation (see below), such as current practices, barriers/facilitators, key issues, and potential solutions in addressing project goals. These data were gathered through qualitative interviews conducted prior to the start of implementation activities, analyzed using a rapid analysis approach [42,43], and shared with EBQI participants to assist in development of local implementation strategies. In addition, EBQI participants were provided local performance data on metabolic monitoring and management, extracted from VA databases as described below for a six-month period prior to the site visit.

During the EBQI Design Phase, EBQI participants consider the QI tools/resources included in the MIAMI Project as well as additional monitoring and management tools and strategies that may be useful for local implementation. The duration of the EBQI Design Phase varies across sites, an understandable phenomenon in implementation studies, where preparation, design and implementation are often classified as distinct phases and differ depending on activities at each intervention site [44].

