### Power analysis

Based on our six EBQI/F intervention sites and six control sites, Table 3 presents detectable slopes (*i.e*., within-phase performance change) and changes in slopes (between phases) assuming first: low, medium and high values for the residual standard deviation (σ), the variances of the random intercepts (*v*_*a*_) and slopes (*v*_*b*_), and a first order auto correlation, ρ, among the observations within a site; then, power of at least 0.8 on a two-sided test made at the 0.05 significance level. Using ASSIST study findings, we estimated residual standard deviations (σ) ranged from 8.9% to 11.9%, *v*_*a*_ from 53.4 to 167, *v*_*b*_ from 4.4 to 6.6, and within-site first order auto correlations (ρ) from 0.10 to 0.53. We used the minimum, midrange, and maximum of the estimates to respectively present best case (σ = 8.9%, *v*_*a*_ = 53.4, *v*_*b*_ = 4.4, ρ = 0.10), expected (σ = 10.1%, *v*_*a*_ = 137.6, *v*_*b*_ = 5.3, ρ = 0.26), and worst case (σ = 11.9%, *v*_*a*_ = 167.0, *v*_*b*_ = 6.6, ρ = 0.53), scenarios. Given the low rates of metabolic monitoring and management observed in preliminary studies, the detectable changes would be both possible and clinically meaningful.

**Table 3 T3:** Detectable differences in slope (% change per month)

**Hypotheses**	**Best case scenario**	**Expected scenario**	**Worst case scenario**
**Implementation has no effect over phase**	3.7%	4.3%	5.1%
**Implementation is no different from control at each phase**	5.3%	6.1%	7.2%

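### The only stated and powered between-arm comparisons are slopes, so a gain completed in the unmeasured Design Phase, or a gain kept through Sustainability, gives no slope signal in the phase concerned; a contrast of phase means should be added

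*Protocol article*

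**What the plan says.** Data analysis defines the comparison: "We will compare the performance change over time (a slope) between EBQI/F and control sites using a random coefficients regression (RCR". It adds that "The RCR will also allow the slopes to change with the phase of the study". The reason given is that "We expect EBQI/F intervention sites to gradually increase performance on monitoring and management measures over time", and that "performance change during pre-implementation is expected to be unchanging or flat, but is expected to increase or trend upward once EBQI/F begins". The data are monthly site rates, "with each site contributing six monthly performance measures in each of the three phases of the study".

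Methods ends Pre-implementation at the first EBQI site visit. That visit begins a planning period that runs "for a variable period of time following the visit (the EBQI Design Phase" and is not one of the three measured phases. Each control site is observed over the same three windows as its matched site. The section on the EBQI/F intervention nevertheless counts the Design Phase as one of the intervention's two components. The EBQI design phase section places site-specific feedback there: "EBQI participants were provided local performance data on metabolic monitoring and management".

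The between-arm row of Table 3 tests "Implementation is no different from control at each phase", with detectable slope differences of 5.3, 6.1 and 7.2 percent per month in the best, expected and worst scenarios.

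**The concern.** The trial asks whether adding EBQI/F raises monitoring and management rates, and it includes a Sustainability Phase to see whether any gain lasts. A slope within a six-month window measures how fast performance is changing, not where it stands. Two patterns that would count as success are therefore hard to see:

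- **Early gain.** If a site reorganises its monitoring after the visit and feedback but before the Implementation window opens, its rate steps up between two measured phases. A separate line per phase absorbs the step in its intercept.
- **Kept gain.** In Sustainability, success is a flat line at a higher level. An unimproved control site is also flat.

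At stake is a non-significant slope comparison being read as no effect, or a fall in slope from Implementation to Sustainability being read as waning, when the gain was made and kept.

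**Working it through.** **Inputs.** From Power analysis: six sites per arm, two-sided 0.05, power 0.80; expected scenario σ = 10.1, v_b = 5.3, ρ = 0.26; best scenario 8.9, 4.4, 0.10; worst scenario 11.9, 6.6, 0.53. From Data analysis: six monthly rates per phase. Assumptions not in the documents: a true gain of 20 points (range 10 to 30), flat control sites, and a Design Phase long enough that residuals in Pre-implementation and Implementation are independent.

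**1. Reproduce Table 3.** Fit a line with its own intercept in each phase. Slope variance per site = v_b + generalised least squares slope variance over six months with AR(1) errors. SE of the arm difference = √(2 × variance / 6). The noncentral-t multiplier for 80% power at 15 df is 3.00.

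| Scenario | Variance per site | SE | Detectable | Table 3 |
|---|---|---|---|---|
| Best | 4.4 + 4.96 = 9.36 | 1.77 | 5.30 | 5.3 |
| Expected | 5.3 + 7.16 = 12.46 | 2.04 | 6.11 | 6.1 |
| Worst | 6.6 + 10.57 = 17.17 | 2.39 | 7.17 | 7.2 |

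Dividing by √2 gives 3.74, 4.32 and 5.07 for the single-group row (stated 3.7, 4.3, 5.1). The 15 df is inferred (6 × 3 − 3); 10 df gives 6.34 in the expected scenario. A continuous piecewise line without phase intercepts does not reproduce the table (3.0 to 5.3 against 6.1). So the powered model appears to be separate lines.

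**2. Expected slope contrasts, EBQI/F minus control, points per month.**

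| True pattern | Pre | Implementation | Sustainability | Level difference in Sustainability |
|---|---|---|---|---|
| A. 20 points gained in Design Phase, held | 0 | 0 | 0 | 20 |
| B. 20 points ramped over Implementation, held | 0 | 20/6 = 3.33 | 0 | 20 |
| C. Half in each, held | 0 | 10/6 = 1.67 | 0 | 20 |
| D. No effect | 0 | 0 | 0 | 0 |

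A and D are identical in every slope and every change in slope. B and D are identical in the Sustainability slope, although B also shows a change in slope of −3.33 from Implementation to Sustainability with the gain fully kept.

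**3. Power of the slope comparison.** The SE implied by Table 3 in the expected scenario is 6.1/2.80 = 2.18.

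- A: power equals the test size, 0.05, whatever the size of the step.
- B: 3.33/2.18 = 1.53; power ≈ Φ(1.53 − 1.96) ≈ 0.33 (best 0.42, worst 0.25). A 10-point ramp has 0.12 and a 30-point ramp 0.63.
- C: the same slope as a 10-point ramp, so about 0.12.

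**4. A contrast of phase means.** Variance of a six-month mean = (σ²/36)[6 + 2Σ(6−k)ρᵏ], k = 1 to 5. In the expected scenario this is 2.834 × 9.267 = 26.26, or 52.5 for a difference of two phases; the random intercept cancels. The multiplier at 10 df is 3.11.

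- No random-slope variance: SE = √(2 × 52.5/6) = 4.18; detectable 13.0 points; power for a 20-point held step 0.99.
- Phase-specific random slopes, months coded 0 to 5 (mean 2.5): 52.5 + 5.3 × (2.5² + 2.5²) = 118.8; SE 6.29; detectable 19.6; power 0.82.
- Months coded 1 to 6 (mean 3.5): 52.5 + 5.3 × (3.5² + 3.5²) = 182.4; SE 7.80; detectable 24.3; power 0.64.

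**5. Sensitivity of that contrast to a purely gradual effect in Implementation.** The mean gain is 2.5 or 3.5 times the monthly slope. With slope variance, the detectable slope is 19.6/2.5 = 7.8 or 24.3/3.5 = 6.9, against 6.3 for the slope test at 10 df. Without it, the range is 13.0/3.5 = 3.7 to 13.0/2.5 = 5.2, against 3.11 × √(2 × 7.16/6) = 4.8.

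**The case against.** The choice of slopes is reasoned. The authors expect a gradual rise once the intervention begins, and the text assigns execution of the local plan to Implementation, with the Design Phase given to planning. Under that expectation the Implementation slope and the change in slope are both non-zero. Read together, rise-then-flat means a kept gain and rise-then-fall a lost one. This stands.

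Pattern A is an extreme: the whole gain must precede Implementation. The outcome windows also blur a late step. A patient counts in the month the window closes, and windows span about 60 days (baseline) or 90 days (follow-up). A change late in the Design Phase would therefore appear partly as an early ramp. This stands too; an exact zero needs the gain to be complete well before Implementation.

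Figure 1 and Additional file 1, which explains the model, are not shown. Phase intercepts may already be fitted; the model that reproduces Table 3 has them. But a fitted intercept is not a planned between-arm test, and the comparisons the article states and powers are slopes. If the model were instead continuous without phase intercepts, a 20-point step would leak into the slopes (about 1 to 2 per month in Implementation), but that model does not match Table 3.

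The level contrast is not free of assumptions either. If intervention sites' gains varied with an assumed SD of 10 points, the detectable difference without slope variance rises from 13.0 to 3.11 × √((52.5 + 52.5 + 100)/6) = 18.2.

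**Conclusion.** The point holds in a limited form. Under the separate-line model, a gain completed in the Design Phase and held gives no slope difference in any phase and is detected only at the 5% test size, and the Sustainability slope alone cannot tell a kept gain from none. The second statement follows from what a slope is. The first rests on the inferred model and on the Design Phase months lying outside the analysed data, as Methods and Data analysis describe. Neither depends on the assumed 20 points; only the power figures do.

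A reader might infer that the planned analysis is null whenever a gain is sustained, or that the trial's single primary contrast cannot detect success. The documents do not support that. A gain that ramps during Implementation still produces a non-zero Implementation slope and change in slope, though with about 33% power for 20 points in the expected scenario. The article names primary outcome measures but no single slope as the primary contrast. This should be fixed; it does not invalidate the plan.

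**What to change.** Keep the slope comparisons. Add to the random coefficients regression a pre-specified EBQI/F minus control contrast of the change in mean monthly rate, (a) from Pre-implementation to Implementation and (b) from Pre-implementation to Sustainability. State its role relative to the slopes, with a hierarchy or multiplicity rule. If Additional file 1 already carries phase-level terms, this needs only the named contrast. Where feasible, extract the Design Phase months from the same databases for each matched pair and treat them as their own segment. For management rates this also means extra chart review.

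The contrast itself uses data already planned for collection, so the main cost is wording. The downsides are one more family of tests and possibly less sensitivity than the slope to a purely gradual effect (6.9 to 7.8 against 6.3 per month when slopes vary between sites). It should therefore supplement the slope and need not replace it.

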**Methods/Design:**

This project employs a cluster randomized clinical trial design to test effectiveness of an evidence-based quality improvement plus facilitation intervention. Eligible study sites were VA Medical Centers with ≥300 patients started on a new antipsychotic prescription in a six-month period. A total of 12 sites, matched in pairs based on scores on an organizational practice survey, were then randomized within pairs to intervention or control conditions.

Study participants include VA employees involved in metabolic monitoring and management of patients treated with antipsychotics at participating sites. The intervention involves researchers partnering with clinical stakeholders to facilitate tailoring of local implementation strategies to address barriers to metabolic side-effect monitoring and management. The intervention includes a Design Phase (initial site visit and subsequent development of a local implementation plan); Implementation Phase (guided by an experienced external facilitator); and a Sustainability Phase. Evaluation includes developmental, implementation-focused, progress-focused and interpretative formative evaluation components, as well as summative evaluation. Evaluation methods include surveys, qualitative data collection from provider participants, and quantitative data analysis of data for all patients prescribed a new antipsychotic medication at a study site who are due for monitoring or management of metabolic side effects during the study phases. Changes in rates of recommended monitoring and management actions at intervention and control sites will be compared using time series analyses.

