We then excluded sites not involved in research, using the Office of Research & Development’s directory of research programs. From those sites located within the contiguous 48 states with active research programs, we contacted the mental health clinical manager at the 24 sites with the lowest proportions of ‘MOVE!’ Program utilization (range 0% to 0.66%). Three of the 24 sites were excluded because of an active or planned research project to study metabolic monitoring and/or management. Two sites were excluded because they already had primary care clinicians integrated into mental health clinics. Two sites declined to participate, and leaders at three other sites did not respond to repeated requests for participation in the project. Leaders at the remaining 14 sites attended conference calls with the study PI to obtain further information, and each agreed to have their site included in the final site selection pool. Each completed a brief survey, adapted from a VA Clinical Practice Organizational Survey that included questions on provider stress and ability to pursue practice change [34,35]. Survey scores ranged from 16.1 to 74.2 on a 100-point scale, with higher scores indicating higher levels of stress and lower capacity to pursue practice change. Sites were ranked according to survey scores. The 12 sites with the highest scores were invited to participate in the study, and all accepted. We used the ranked list of sites to identify matched pairs with comparable survey scores, and then randomly selected one site from each pair to receive the intervention, using a random number generator tool available at http://www.random.org. The mean survey score of the intervention sites was 48.9 compared to 51.1 for the control sites. Shortly after this matching, two of the sites withdrew from study participation; however, fortunately, the remaining two sites that had not initially been selected for study inclusion agreed to participate. Both of these sites had low scores on the Clinical Practice Organizational Survey, and thus did not affect the distribution of intervention and control sites on this inclusionary variable. Soon after this change, another site withdrew from the study; however, this occurred at about the same time that one of the previous sites that had earlier declined participation was now willing to participate. Both of these sites had been randomized to the intervention arm, and so the newly available site replaced the withdrawn site, resulting again in 12 sites participating in the study: 6 intervention sites and 6 control sites.

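### The article's model carries neither the matched pair nor the matching score, and its claim that the first two site replacements left the arms unaffected has no figures behind it

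*Protocol article*

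**What the plan says.** **Design.** The abstract says that the sites were "matched in pairs based on scores on an organizational practice survey, were then randomized within pairs to intervention or control conditions". Site selection describes ranking sites by score, forming pairs with comparable scores, and then "randomly selected one site from each pair to receive the intervention". In Methods, the phase dates are tied to the pair: "Each control site will be examined over the same three six-month periods as the matched intervention site". The same section describes the design "with matched pairs of VA facilities defined as the clusters".

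**Analysis.** Data analysis describes a random coefficients regression (RCR) with repeated measures within a site and, between sites, only variation within an arm: "The random coefficients portion of the RCR accounts for site-to-site variability within an intervention group". For the full model the reader is told to "see Additional file 1 for detailed explanation"; that file is not available here. The covariate section lists patient demographics and diagnoses summarised by site. It does not list the survey score. The power section starts from "Based on our six EBQI/F intervention sites and six control sites" and uses four inputs (residual SD, random-intercept variance, random-slope variance, autocorrelation), none of them for pairs. Yet the Background, where it introduces this project, gives the reason for stratifying on the score: organisational context is expected to predict implementation success strongly.

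**Replacements.** Fourteen sites were surveyed, with scores from 16.1 to 74.2, and the 12 highest were taken. Arm means at randomisation were 48.9 (intervention) and 51.1 (control). Two sites then withdrew and the two unselected sites came in. Of these the article says that they had low scores and "thus did not affect the distribution of intervention and control sites on this inclusionary variable". A third withdrawal followed, filled by a site said to have been randomised to the same (intervention) arm. No later arm means, final pairs or assignment rule for the two low scorers are given.

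**The concern.** A factor that restricted the randomisation, and that is expected to predict the outcome, normally belongs in the analysis, either as the pair or as the score itself. As described, the model has neither. If paired sites are alike, through similar scores or shared calendar dates, that likeness stays in the error term and the standard error of the slope difference is too wide.

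The replacements make the score matter more. Sites from the top 12 gave way to the two lowest of 14. An arm that received one of them will normally have a lower mean than before. Balance survives only if the falls are similar in both arms, and the article shows nothing on this. The two printed means describe an allocation that no longer exists, so a reader cannot tell how well the arms match on the one variable chosen for matching.

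**Working it through.** **1. Does Table 3 take credit for pairing?**

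Inputs (Power analysis; Data analysis): 6 sites per arm, 6 monthly values per phase, two-sided 0.05, power 0.80, and the stated σ, v_a, v_b and ρ.

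Ratio of the second row (difference from control) to the first (one arm): 5.3/3.7 = 1.43, 6.1/4.3 = 1.42, 7.2/5.1 = 1.41. All are about √2 = 1.414, the factor for two independent arms.

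Full reproduction: the variance of one site's estimated slope is the slope element of (X'V⁻¹X)⁻¹, with V = X·diag(v_a, v_b)·X' + σ²·AR(1) over six months. This gives 9.36 / 12.46 / 17.17 (best / expected / worst). The detectable slope is m·√(var/6) for one arm and m·√(2·var/6) for the difference. The article does not state degrees of freedom. With 16 df assumed (m = 2.985):

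| | Best | Expected | Worst |
|---|---|---|---|
| One arm, computed (stated) | 3.73 (3.7) | 4.30 (4.3) | 5.05 (5.1) |
| Difference, computed (stated) | 5.27 (5.3) | 6.08 (6.1) | 7.14 (7.2) |

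All six cells stay within 3% for 14 to 22 df. Table 3 therefore rests on independent arms with no pair component.

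**2. What does leaving out the pair do?**

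The within-pair correlation c of site slopes is not given, so it is varied. Simulated type I error of an unpaired 10-df test on site slopes: 0.050 (c = 0), 0.041 (c = 0.1), 0.025 (c = 0.3), 0.013 (c = 0.5). The test is conservative.

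**3. Would fixed pair effects help?**

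That analysis has 5 df (m = 3.51) instead of 10 (m = 3.11). Expected-case detectable difference, m·√(2·12.46·(1−c)/6):

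| Analysis | Detectable difference, % per month |
|---|---|
| Unpaired, 10 df | 6.34 |
| Paired, c = 0 | 7.16 |
| Paired, c = 0.1 | 6.79 |
| Paired, c = 0.2 | 6.40 |
| Paired, c = 0.3 | 5.99 |
| Paired, c = 0.5 | 5.06 |

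Break-even is c = 1 − (3.11/3.51)² ≈ 0.22. Against the 16 df that best reproduce Table 3 it is 1 − (2.985/3.51)² ≈ 0.28.

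**4. What does adjusting for the score cost?**

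About 1 df: the expected-case detectable difference moves from 6.34 (10 df) to 6.42 (9 df), before any gain from explained variance. This assumes that the score is not strongly associated with arm; a real imbalance would add to the cost.

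**5. How far could the replacements move an arm mean?**

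The 12 highest of 14 were selected, so the two left over are the two lowest and one of them holds the minimum, 16.1. The mean of the original 12 is (48.9 + 51.1)/2 = 50.0. One site in an arm of six changes the mean by (old − new)/6:

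- site scoring 30: (30 − 16.1)/6 = 2.3 points
- site scoring 50: (50 − 16.1)/6 = 5.65, or 5.7 points
- site scoring 74.2: (74.2 − 16.1)/6 = 9.7 points

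The gap between arms at randomisation was 51.1 − 48.9 = 2.2. The scores 30 and 50 are illustrations; 74.2 is the stated maximum. These are shifts in one arm from one replacement. The second low score, the withdrawn sites' scores and the arms entered are not given, so the net change in the gap cannot be computed.

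**The case against.** The strongest reply is that the article condenses a fuller document. Additional file 1 may contain a pair term, and an article need not repeat it. That stands: what can be said is only that the article's model text, covariates and power inputs name neither pair nor score. A second reply also stands: ignoring pairs with six sites per arm is a legitimate choice, and fixed pair effects would lose power unless slopes within pairs correlate above roughly 0.22 to 0.28.

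Several stronger readings are tempting and are not supported:

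- **Biased arm contrast.** One might infer that the ongoing national programme or seasonality leaks into the comparison because pairs start at different times. But each control site uses its matched site's dates. With equal data per site, a calendar effect shared by a pair enters both arms equally and cancels. Only the standard error is affected.
- **False positives.** Step 2 shows the opposite.
- **An established imbalance.** If one low scorer entered each arm, the shifts could largely offset, and the article's sentence, which concerns the distribution between arms, could be true. It is unsupported, not shown to be false.
- **A claim about all three swaps.** The sentence covers only the first two replacements and only the survey score, not the pairing.
- **Broken matching.** If the returning site was one of the first two to withdraw, as its having been randomised suggests, ten original sites remain and two or three of the six pairs changed. Whether current partners have similar scores, or pairs were re-formed, is not stated.
- **Pairs named as clusters.** This is loose wording. Randomisation and analysis are described by site elsewhere, and no result depends on it.

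**Conclusion.** The point holds as a moderate one with two parts.

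First, the described analysis does not reflect the matched randomisation, through either the pair or the score. The cost is lost precision if pairs are alike (actual type I error about 0.025 instead of 0.05 at an assumed correlation of 0.3) and no protection against chance or replacement-induced imbalance on the score. This is conditional on Additional file 1 not already containing such a term.

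Second, the statement about the first two replacements is a non sequitur, and the printed means are out of date. This does not depend on any unseen file. A single replacement could move an arm mean by 2.3 to 9.7 points under the illustrated scores, against a gap of 2.2 at randomisation; the true figure is unknown.

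Neither part makes the planned comparison invalid.

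**What to change.** 1. Add each participating site's actual survey score to the RCR, with its interaction with time because the quantity tested is a slope. Cost: about 1 df (6.34 to 6.42 in the expected case). The score has already been collected for the 14 surveyed sites. If the returning site declined before the survey, say so and state how its score is obtained.
2. As a sensitivity analysis, add a random pair effect on intercept and slope, using the final pairs. Do not use fixed pair effects, which leave 5 df.
3. List the final pairs, the 12 scores, and the rule that placed the two low-score sites in an arm. Say which site returned in the third swap.
4. Replace 48.9 and 51.1 with the arm means of the 12 participating sites, and either support the statement about an unaffected distribution with those means or delete it.
5. State in the article whether Additional file 1 includes the pair. Naming the site as the cluster is an optional wording change.

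The trial is reported as being early in its Implementation Phase, so all of this can be settled before outcomes are analysed. It needs some model wording and a short table, and no new data unless a site lacks a score.
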